#### Cost-effectiveness

A cost-effectiveness analysis will be performed at the end of the implementation phases. Costs of each component of *Break Free* will be tracked, including pharmacotherapy, patient liaison time and training, TTS time and training, telephone and material costs, incentives, and other administrative costs. We will value the costs of each activity using standard costs. Cost-per-quit estimates will be calculated.

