**Methods:**

The broader program, the *Take CARE* study, is a multi-site research collaborative designed to address three risk factors for cervical cancer incidence and mortality: tobacco use, human papillomavirus (HPV) infection, and cervical cancer screening. *Break Free* is a primary care clinic-based implementation program that aims to promote smoking cessation among female smokers in Appalachia by standardizing clinical practice protocols. *Break Free* includes: (1) implementation of a tobacco user identification system in the Electronic Health Record, (2) clinic staff and provider training on the Ask, Advise and Refer (AAR) model, (3) provider implementation of AAR to identify and treat women who want to quit smoking within the next 6 months, (4) facilitated access to cessation phone counseling plus pharmacotherapy, and (5) the bundling of *Break Free* tobacco cessation with HPV vaccination and cervical cancer screening interventions in an integrated approach to cervical cancer prevention. The study spans 35 Appalachian health clinics across 10 healthcare systems. We aim to enroll 51 adult female smokers per health system (total N = 510). Baseline and follow-up data will be obtained from participant (provider and patient) surveys. The primary outcome is self-reported 12-month point prevalence abstinence among enrolled patients. All randomized patients are asked to complete follow-up surveys, regardless of whether they participated in tobacco treatment. Data analysis of the primary aims will follow intent-to-treat methodology. Secondary outcomes will assess program implementation and cost effectiveness.

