### Hybrid effectiveness-implementation study design

In this cluster randomized trial, health systems are stratified by state and then randomized in a 1:1 ratio to either an Early Arm or Delayed Arm. To reduce the risk for contamination, within each stratum, health systems are randomized into Early Intervention or Delayed Intervention arms. All clinics within each health system are randomized to the same condition (Early or Delayed Intervention). Neither health systems nor study participants are blinded to their intervention assignment.

Figure 2 outlines the timeline for study implementation and evaluation. Following a planning phase (months 1–23; not shown in the figure), *Break Free* will be implemented in Early Arm health systems over a 12-month period. After this 12-month period ends, research staff will train Early Arm health systems on how to bill for brief counseling (AAR) and smoking cessation phone counseling, as well as how to implement *Break Free* using their own staff and resources as they transition to a full sustainability period. During this period, Early Arm health systems will also learn how to “bundle” all three *Take CARE* projects addressing smoking cessation, HPV vaccination, cervical cancer screening as part of an integrated cervical cancer prevention program disseminated by clinics. Delayed Arm health systems will initially enroll female smokers into an observational study, which will allow estimation of the smoking cessation rate in the target population receiving usual care. This group of women will serve as the comparison for the “effectiveness” of *Break Free*. After 12 months, while the Early Arm health systems are in the sustainability period, Delayed Arm health systems will implement *Break Free*, delivered by our research staff. After that 12-month period ends, they too will then shift to a sustainability period. Implementation of *Break Free* will be evaluated through randomly sampled patient assessments of provider fidelity to AAR and, for women enrolled in *Break Free* TTS counseling, assessments of TTS fidelity to *Break Free* counseling.

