#### Delayed Arm health systems

While the Early Arm health systems are in the Early Intervention phase, the Delayed Arm health systems will continue usual care (Fig. 1). During this phase, to determine “usual care” tobacco-related outcomes in the Delayed Intervention arms, providers will ask eligible female smokers about their tobacco use and assess readiness to quit. Female smokers who are interested in quitting in the next 6 months will be asked to participate in this observational component of the study. Those who agree to participate will be given either a paper a baseline survey packet with a consent script to sign and the baseline survey in the clinic, where they will be asked to complete it in the clinic and then mail it to the research team (a self-addressed stamped envelope will be included), or an online link with an electronic consent and survey. The consent will include language about follow-up surveys at 3, 6, and 12 months. Study staff will call or email Delayed Arm participants at 3-, 6-, and 12-months post-baseline to assess smoking behaviors. Participants will receive a $10 gift card incentive for completion of each survey. Once Delayed Arm clinics begin the Active Intervention phase, they will follow all procedures implemented in Early Arm health systems as described above.

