#### Sustainability evaluation

*Sustainability* will be measured by: (1) documentation of patient tobacco use status in the EHR; (2) TTS self-report of continued smoking cessation counseling; and (3) billing-related documentation of number of counseling sessions billed for overall and for each smoker who has at least one *Break Free* counseling session. The Survey and Data Collection core will support EHR and billing data extraction. With the support of the Biostatistics and Evaluation core, we will also assess cost-effectiveness by considering costs of each component including pharmacotherapy, clinic counselor time and training, smoking cessation counselor time and training, telephone and material costs, and other administrative costs.

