### Sample size and power analysis

The sample size for the primary outcome (i.e., smoking cessation among female smokers) is 51 female smokers per health system, for a total of 510 participants. This sample size is based on a two-sample test of the 7-day point prevalence abstinence at 6 months with power calculated using a standard cluster randomized design formula [44]. Assuming a 10% quit rate in the delayed group, a 25% quit rate in the early intervention group, and a conservative estimate of the intraclass correlation of 0.017, a total of 10 health systems, equally randomized to Early and Delayed Intervention groups, a total of 43 smokers per health system will provide 80% power at a two-sided significance level of 5%. The sample size was inflated to 51 smokers per health system (or 510 total) to account for an estimated 20% dropout.

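### The planned cost-per-quit is not tied to the randomised usual-care comparison; taken over all Break Free quits, it would fall 40% below the cost per additional quit at the planning rates if usual care cost nothing

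*Protocol article*

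**What the plan says.** The Abstract gives cost effectiveness secondary-outcome status: "Secondary outcomes will assess program implementation and cost effectiveness".

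Two sections describe the analysis. Under Sustainability evaluation: "we will also assess cost-effectiveness by considering costs of each component including pharmacotherapy, clinic counselor time and training", followed by further programme items. Under Statistical analyses, Cost-effectiveness: "Costs of each component of *Break Free* will be tracked, including pharmacotherapy, patient liaison time and training, TTS time and training", again followed by further programme items. That section sets the timing ("A cost-effectiveness analysis will be performed at the end of the implementation phases") and closes with its one output, "Cost-per-quit estimates will be calculated". Neither section mentions the Delayed Arm, usual-care costs, a difference between arms or an additional quit.

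Elsewhere the comparator is explicit. In the Early Arm's intervention period, "the Delayed Arm health systems will continue usual care (Fig. 1"). The study design section says of the women enrolled there: "This group of women will serve as the comparison for the “effectiveness” of *Break Free". Patient outcomes, under Statistical analyses, then models cessation in Early against Delayed Arm systems.

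**The concern.** Cost effectiveness asks what it costs to gain one more quit than usual care would have produced. The trial randomises health systems so that this gain can be estimated, and its sample size assumes that a tenth of usual-care women will quit. A ratio of programme cost to all quits among programme women ignores that tenth. It also cannot register failure, because a programme with no effect still returns a finite cost per quit.

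The timing adds to the ambiguity. The analysis follows the implementation phases, in the plural. By then the Delayed Arm systems have also delivered Break Free, while the Early Arm is in its sustainability period. Women treated in that second phase have no concurrent usual-care group, so a figure pooled over both phases would move further from the randomised contrast.

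The result matters because cost-effectiveness is part of the sustainability evaluation, and overall results are to be presented to the boards of the participating health systems. A board could read a low average as the price of a quit gained.

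**Working it through.** **Inputs**
- Quit rates, from Sample size and power analysis: "Assuming a 10% quit rate in the delayed group, a 25% quit rate in the early intervention group". So p0 = 0.10 and p1 = 0.25, for 7-day abstinence at 6 months.
- Women per arm: 5 systems × 51 = 255.
- C is the Break Free cost per enrolled woman. It is left symbolic because the article gives no amount.
- f is the usual-care cost per woman as a fraction of C. The article does not give it, so f is an assumption, shown from 0 to 0.5.

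**The plan's own figure.** The article states no cost-per-quit figure to reproduce. The figure that rests on these rates is the 80% power with 43 women per system and an intraclass correlation of 0.017:
- Design effect = 1 + 42 × 0.017 = 1.714.
- Standard error = √[(0.10 × 0.90 + 0.25 × 0.75) × 1.714 / 215] = 0.0470.
- A cluster-level t-test on 8 degrees of freedom gives 79.7%.

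The stated power is therefore consistent with 10% and 25%.

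**Two possible ratios**
- Average cost per quit = C / p1
- Incremental cost per additional quit = (C − fC) / (p1 − p0)
- Shortfall of the average = 1 − average / incremental, which equals p0 / p1 when f = 0

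**At the planning rates with f = 0**
- Quits among 255 Break Free women: 255 × 0.25 = 63.75
- Quits expected under usual care: 255 × 0.10 = 25.5
- Additional quits: 63.75 − 25.5 = 38.25
- Average: C / 0.25 = 4.00C
- Incremental: C / 0.15 = 6.67C
- Shortfall: 1 − 4.00 / 6.67 = 40%

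**Varying the quit rates (f = 0)**

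| Usual care | Break Free | Shortfall of the average |
|---|---|---|
| 5% | 25% | 20% |
| 10% | 30% | 33% |
| 10% | 25% | 40% |
| 10% | 20% | 50% |
| 15% | 25% | 60% |
| 10% | 15% | 67% |

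**Varying usual-care cost (10% versus 25%; average fixed at 4.00C)**

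| f | Incremental | Shortfall of the average |
|---|---|---|
| 0 | 6.67C | 40% |
| 0.1 | 6.00C | 33% |
| 0.2 | 5.33C | 25% |
| 0.3 | 4.67C | 14% |
| 0.4 | 4.00C | 0% |
| 0.5 | 3.33C | average is 20% above |

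**No effect (10% versus 10%).** The average is C / 0.10 = 10C. The incremental ratio has a zero denominator, which is the right signal that nothing was gained.

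**The case against.** The strongest reply is that the article does not define the denominator. In a trial whose effectiveness comparison is Early against Delayed, an analysis labelled cost-effectiveness can reasonably be read as using the same contrast. The section is only four sentences long, and the exact form of the ratio may be set out in a full protocol or analysis plan that is not shown.

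Much of this stands. A reader might infer that the plan prescribes a ratio crediting the programme with usual-care quits and so understates cost by 40%. The article does not support that: the all-quits denominator is the plain reading of an undefined term, not a stated method. Nor is costing the programme alone the error. Programme cost divided by additional quits is a valid incremental ratio when usual care costs little; any bias comes from the denominator. The 40% also needs the planning rates to hold and usual care to cost nothing. Finally, the article does not say that usual-care costs or Delayed Arm pharmacotherapy use are collected. Pharmacotherapy use is listed as an outcome for Break Free participants only.

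What does not fall away is the gap in the text itself. Two sections settle the cost inputs and one names the output, and neither uses the comparator that the article sets up for effectiveness. Interval methods and missing-data handling for the ratio can be left to an analysis plan; which ratio is meant decides what the secondary outcome measures.

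**Conclusion.** The point holds in conditional form. The cost-per-quit output is not linked to the randomised usual-care comparison, and its plain reading is an average that includes quits expected without the programme. If computed that way, it is 40% below the cost per additional quit at 10% versus 25% with zero usual-care cost. The rate pairs shown give 20% to 67%. At the planning rates the gap closes as usual-care cost rises to 0.4C and reverses above that. The planning rates refer to 6 months, whereas the Abstract puts the primary outcome at 12 months, so these figures illustrate the size of the problem and do not forecast the result. The point concerns a secondary outcome and leaves the primary comparison untouched, but it should be settled before costs are reported.

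**What to change.** In the Cost-effectiveness section, state that the measure is the incremental cost per additional quit: the difference in mean cost per woman divided by the difference in abstinence, Early Arm Break Free against concurrent Delayed Arm usual care, at the primary outcome time point, named explicitly. Set the Delayed Arm programme cost to zero for the main figure and show a sensitivity range for usual-care cost, because the article does not say such costs are collected. Report the average cost per quit as descriptive only.

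This takes a sentence or two of text and slightly more analysis. The quit data are already planned in both arms. The drawback is a less favourable headline figure wherever usual-care cost is small relative to Break Free.

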#### Sustainability

We will track the rate at which women are referred to counseling and the billing for cessation counseling. Initial analyses will use hierarchical models for count data, more specifically, negative binomial regression models, to estimate the trends over time. Subsequent analyses will use ‘interrupted time series analysis’ [48] to track the changes in rates of referrals and billing for smoking cessation over time. These analyses will estimate the effect of policy changes at the health system and health center levels on these rates, accounting for the longitudinal design and for potential seasonal cycles in referrals and smoking cessation counseling.

### Data management and monitoring

Outcome measures (smoking-related, provider, sustainability) will be obtained from self-administered patient surveys (in clinic, online) and TTS-delivered phone assessments, provider surveys (in clinic, online), and review of medical charts using electronic health records. We will use REDCap as our data entry system for these data.

A Data and Safety Monitoring Board (DSMB) for the overarching *Take CARE* program will review protocol and monitor study progress and outcomes, make recommendations, and ensure that data and human safety requirements are met. The DSMB is comprised at least five individuals, including clinicians and researchers experienced in implementation science, clinical trials, and cervical cancer; a clinical biostatistician, and a layperson patient advocate. No members of the DSMB is associated with the three initiatives that comprise the overall *Take CARE* research program.

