Cessation phone counseling is led by a trained TTS. A study-supported TTS is available to all participating clinics during the intervention phase. The TTS is a bachelor’s-level provider who has completed a certified tobacco treatment training program. If a health system has a dedicated TTS, that TTS will be trained in the *Break Free* protocol by the study TTS prior to working with *Break Free* participants. Four counseling calls are included in *Break Free*. During each call, a trained TTS uses motivational interviewing techniques to bolster intention and confidence around smoking cessation, guide smokers through a quit attempt and help them strategize for relapse prevention. The TTS tracks participants’ quit date, smoking cessation outcomes, pharmacotherapy use, and session content. Side effects of pharmacotherapy are monitored during counseling calls. Participants whose side effects are not managed with the usual recommendations (e.g., do not wear an NRT patch at night, rotate NRT patches daily) will be referred to their provider at the clinic. The TTS will call the clinic to notify the provider that the participant is experiencing a side effect that is difficult to manage. If a patient experiences a serious adverse effect in response to pharmacotherapy, that information will be conveyed to the study research team and reported to the IRB.

The *Break Free* delivery model includes a standard counseling program for smokers ready to quit in the next 30 days and a modified counseling program for smokers who are ready to quit in the next 6 months, but not in the next 30 days. *Break Free* offers efficacious strategies [43] regardless of participants’ immediate willingness/readiness to quit (Table 1). The first *Break Free* phone counseling session addresses smoking rate reduction for all participants. Rate reduction occurs by using strategies such as breaking brand loyalty, self-monitoring, and disrupting automatic triggers to smoke. The content of the remaining three phone counseling sessions depends on whether the participant is ready to quit in the next 30 days or not. Session topics and goals are included in Table 1. In summary, the standard program guides a smoker through the quitting process by setting a quit date and creating a relapse prevention plan. The modified program includes goals for reductions in the frequency and amount of smoking between each call.

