Recruitment, Enrollment, and Consent of Participants: Figure 3 outlines the process for participant recruitment and enrollment into the early arm intervention. Eligible patients will be identified during routine clinic visits. Providers will ask patients about tobacco use and advise smokers to quit. Women who are interested in quitting within the next 6 months and are eligible for *Break Free* will receive a prescription for pharmacotherapy and referral to the Enrollment Specialist for that clinic or health system. The Enrollment Specialist will introduce potential participants to the *Break Free* program, distribute the patient educational materials, and collect patient contact information for referral to the study-specific TTS to be consented into the study.

Within a week, the study-specific TTS will contact potential participants and obtain verbal informed consent. If the TTS is unable to reach the potential participant, they will attempt to reach them up to ten times to schedule the informed consent and baseline assessment. Consented participants’ contact information is entered into RedCap data management system for secure storage. Contact information is used to connect participants to *Break Free* phone counseling calls and for follow-up assessments. All participants are assigned a subject ID, which is stored in RedCap independently from participant data. After consent is obtained, the study specific-TTS will administer the baseline assessment via phone. Participants will receive $10 for completing the baseline assessment.

Counseling and pharmacotherapy: The *Break Free* 4-session counseling protocol begins after the baseline assessment is complete. The study-specific TTS will counsel participants from health systems that do not have a dedicated TTS on staff; otherwise, the health system’s TTS will perform the counseling. Again, if the TTS is unable to reach participants for a counseling session, they will call them up to ten times to reschedule. If a participants’ phone number is not working, then the TTS will send a follow-up email and, if needed, a mailed letter, to update participant contact information.

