Fidelity assessments: Fidelity to the intervention by providers and the TTS will be assessed separately. To assess provider fidelity to the AAR model, each quarter during a 1-week period, all patients who visit the clinic will be asked to complete an anonymous, self-report, post-provider visit survey. Paper surveys will be collected in a sealed envelope by the check-out staff person at the clinic and mailed to the study team by the Clinic Champion. Patients will also have the option to complete an online survey by scanning a QR code.

To assess TTS fidelity to *Break Free*, ten percent of all *Break Free* participants will be randomly selected and called after a scheduled counseling call to confirm the call occurred and to determine which content was discussed. No financial or other incentives are given for the fidelity assessments.

Patient follow-up assessments: *Break Free* participants will be contacted at 3-, 6-, and 12-months post enrollment to assess current tobacco use and quit attempts via online or phone surveys. Participants will receive a $10 gift card incentive for completion of each follow-up survey. Two weeks prior to each follow-up survey, participants will be sent a proactive reminder email or mailed letter reminding them of the upcoming follow-up assessment.

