##### Patient outcomes

The primary outcomes among *Break Free* patient participants include self-reported: (1) 7-day point prevalence abstinence; (2) 7-day floating abstinence during any period since last assessment; (3) prolonged abstinence (no smoking after a 2-week grace period after the quit date); and (4) at least one 24-h quit attempt. A 24-h quit attempt is an important endpoint given that it is associated with a greater likelihood of future cessation [39]. Secondary outcomes among *Break Free* participants include use of pharmacotherapy and number of counseling sessions completed.

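### As written, self-reported smoking is followed up differently in the two arms, which may bias the unblinded comparison toward Break Free

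*Protocol article*

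**What the plan says.** **Who collects outcomes.** Under Data management and monitoring, outcome measures, smoking-related ones included, "will be obtained from self-administered patient surveys (in clinic, online) and TTS-delivered phone assessments". The sentence names neither arm nor visit. Under Patient components, the TTS delivers the counseling and tracks each participant's "quit date, smoking cessation outcomes, pharmacotherapy use, and session content". In the Early Arm the TTS also takes consent and gives the baseline: "After consent is obtained, the study specific-TTS will administer the baseline assessment via phone".

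**Early follow-up.** The Procedures section sets it out thus: "participants will be contacted at 3-, 6-, and 12-months post enrollment to assess current tobacco use and quit attempts via online or phone surveys". No assessor is named. The same paragraph adds: "Two weeks prior to each follow-up survey, participants will be sent a proactive reminder email or mailed letter".

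**Delayed (usual-care) follow-up.** Under Delayed Arm health systems: "Study staff will call or email Delayed Arm participants at 3-, 6-, and 12-months post-baseline to assess smoking behaviors". No reminder is described. Early Arm procedures extend to Delayed clinics only once they enter their Active Intervention phase, so not to the comparison cohort.

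**Prolonged abstinence.** Outcome evaluation, Patient outcomes, lists among the primary outcomes "prolonged abstinence (no smoking after a 2-week grace period after the quit date". Statistical analyses, Patient outcomes, includes it among the binary outcomes compared between Early and Delayed Arms. In Table 1 the standard track sets a quit date at session 2. The rate-reduction track only discusses a future quit at that point, and encourages a target date at session 4.

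**Context.** The trial is unblinded (Hybrid effectiveness-implementation study design) and relies on self-report (Limitations). Statistical analyses, Patient outcomes, counts survey non-responders as continuing smokers, while Missing data plans multiple imputation of missing outcomes.

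**The concern.** With no biochemical check and no blinding, the comparison is only as fair as the way the question is put in each arm. Three features differ by arm as written.

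- A reminder before each survey should raise response. If it goes to one arm and silence is scored as smoking, that arm gains apparent quitters without anyone quitting.
- If the counselor asks the outcome question, a woman may be less willing to admit smoking to the person who helped her try to stop. Usual-care women have no such relationship with the study staff who contact them.
- Prolonged abstinence is tied to an event that the intervention creates. Usual-care women are given no quit date, so the same words can describe different outcomes in the two arms.

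The plausible direction of the first two is toward Break Free. The third makes one listed primary outcome hard to interpret, with no clear direction.

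**Working it through.** The article gives no response or misreport rate by arm, so there is no figure of its own to reproduce on this point. Its only benchmarks, under Sample size and power analysis, are quit rates of 10% and 25% (a 15-point difference) and 20% dropout, not split by arm.

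**1. The two arms side by side**

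| Feature | Early (Break Free) | Delayed (usual care) |
|---|---|---|
| Visits | 3, 6, 12 months | 3, 6, 12 months |
| Incentive per follow-up survey | $10 | $10 |
| Mode | online or phone | call or email |
| Assessor | not named; TTS-delivered assessments are listed as an outcome source | study staff |
| Reminder before each survey | yes, two weeks ahead | none described |
| Quit date from the programme | session 2 (standard); encouraged at session 4 (rate reduction) | none |

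Schedule and incentive match, and mode is close. Reminder and quit date differ as described. The assessor may differ.

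**2. Unequal response, non-responder = smoker**

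Let q be the true quit rate, equal in both arms, and r the response rate, unrelated to quitting. The observed rate is q × r, so the spurious difference is q × (r_Early − r_Delayed). Assumed values:

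| q | 85% vs 70% response | 90% vs 60% response |
|---|---|---|
| 10% | 0.10 × 0.15 = 1.5 points | 0.10 × 0.30 = 3.0 points |
| 15% | 0.15 × 0.15 = 2.25 points | 0.15 × 0.30 = 4.5 points |

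**3. False reports in one arm**

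Assume that 5% of Early smokers who respond say they have quit, with 15% true quitting and 85% response. Among all Early women this adds 0.05 × (1 − 0.15) × 0.85 = 0.036, or 3.6 points. With the 2.25 points from step 2 at the same quit rate and response split, the total is about 5.9 points.

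**4. Effect on the test**

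The planned design has 5 systems of 43 evaluable women per arm and an intraclass correlation of 0.017. The design effect is 1 + 42 × 0.017 = 1.714, and the effective size is 5 × 43 / 1.714 = 125.4 per arm. Take 10% true quitting in both arms, everyone responding, and false reports by 0% of Delayed and 5% of Early smokers. The observed rates are 10% and 10% + 0.05 × 90% = 14.5%, a difference of 4.5 points. The standard error is √[(0.10 × 0.90 + 0.145 × 0.855) / 125.4] = 4.1 points. The two-sided 5% test then rejects about 19% of the time (normal approximation; allowing for only ten clusters would give somewhat less). With 2% against 5% false reports the difference is 2.7 points and the rejection rate about 10%.

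**5. Prolonged abstinence**

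The definition needs a quit date. A standard-track Early woman gets one early in counseling. A rate-reduction woman may reach session 4 without one. A usual-care woman has one only if she chose it herself. The article does not say what counts as the quit date for the last two groups, yet the outcome is to be compared between arms.

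**The case against.** **Counselor collection is inferred.** A reader might conclude that the TTS collects the Early 3-, 6- and 12-month outcomes. The article does not say so. The sentence under Data management and monitoring pools smoking, provider and sustainability measures. Its TTS assessments could be the Early baseline, records from the counseling calls, or the secondary outcomes of pharmacotherapy use and sessions completed. This stands. What remains is that the sentence concerns outcome measures and that nothing in the article keeps the counselor away from the endpoint.

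**Follow-up clocks.** A reader might also see a timing difference between post-enrollment and post-baseline visits. There is essentially none: in the Early Arm the TTS gives the baseline once consent is obtained. The anchor problem concerns only the quit date in prolonged abstinence.

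**Prolonged abstinence is one outcome of several.** Point prevalence, which is the abstract's primary outcome and the basis of the sample size, needs no quit date. Usual-care women can report a quit date of their own, and the survey items are not shown. This limits the reach of the point but does not remove it, because the article lists the outcome as primary and commits to comparing it.

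**Missing-data rule.** The arithmetic in step 2 follows only from scoring non-responders as smokers. The Missing data section plans multilevel imputation with intervention group in the model, and under that rule the calculation does not apply in this form. The two sections conflict, so it is unclear which governs. Imputation would not correct false reports.

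**Disclosure.** Limitations acknowledges observation bias and social desirability, and defends self-report on practical grounds. It does not mention that collection differs by arm, which is avoidable without biochemical testing.

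**Conclusion.** The point holds in conditional form: the described follow-up is not the same in the two arms and may bias the comparison toward Break Free. That a reminder is described for one arm only, and that the quit date comes from the programme, are in the text. Counselor-collected follow-up is a reading that the text allows.

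Under the assumed rates, unequal response is worth about 1.5 to 4.5 points if non-responders count as smokers, and one-sided false reporting about 3.6 points more. Against a planned 15 points this is small to moderate. It would not by itself produce the planned effect, but it could inflate a modest one or raise the false-positive rate. The documents do not support saying that the result will be biased, or by how much, because they give no response or misreport rates by arm. No sample-size figure changes.

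**What to change.** - State that the 3-, 6- and 12-month outcome surveys in both arms are self-administered or conducted by existing study staff other than the TTS, with the same mode order, reminders and number of contact attempts. The visit schedule and the $10 payment already match and need no change.
- Treat TTS call records as process data only, and amend the sentence under Data management and monitoring accordingly.
- Define prolonged abstinence from an anchor that exists in both arms, for example a fixed interval after enrolment, and ask it with the same items.
- Say which missing-data rule governs the primary comparison, since the effect of unequal response depends on it.

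The cost is reassigning some calls among existing staff, sending reminders to Delayed women, and minor edits to the text and surveys.
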